### Appendix 3 SLE Flare Scoring Index

| Mild or Moderate Flares                                                                                                                                                                                                                                                                                                                                                                                                                                                                                                                                                                                        | Severe Flare                                                                                                                                                                                                                                                                                                                                                                                                                                                                                                                                                                                                                                                                                                                                                                                           |
|----------------------------------------------------------------------------------------------------------------------------------------------------------------------------------------------------------------------------------------------------------------------------------------------------------------------------------------------------------------------------------------------------------------------------------------------------------------------------------------------------------------------------------------------------------------------------------------------------------------|--------------------------------------------------------------------------------------------------------------------------------------------------------------------------------------------------------------------------------------------------------------------------------------------------------------------------------------------------------------------------------------------------------------------------------------------------------------------------------------------------------------------------------------------------------------------------------------------------------------------------------------------------------------------------------------------------------------------------------------------------------------------------------------------------------|
| 
... A change in SELENA-SLEDAI score of 3 points or more (but not exceeding 12 points)
 
... New/worsening:
 
 
Deep photo-sensitive discoid erythema
 
Cutaneous vasculitis and blisters
 
Nasopharyngeal ulcer
 
Pleurisy
 
Pericarditis
 
Arthritis
 
Pyrexia (due to SLE disease activity)
 
 
... Prednisone dose increased, but not exceeding 0.5 mg/kg/day
 
... NSAIDs or hydroxychloroquine added for active SLE
 
... An increase of 1.0 or more, but no more than 2.5, in PGA score
 | 
... SELENA-SLEDAI score change greater than 12
 
... New/worsening:
 
 
Central nervous system manifestations—systemic lupus erythematosus
 
Vasculitis
 
Nephritis
 
Myositis
 
Platelet count < 60,000
 
Hemolytic anaemia: hemoglobin < 70 g/L or a decrease in hemoglobin > 30 g/L
 
 
Require: Double the dose of prednisone, or increase prednisone to >0.5 mg/kg/day, or hospitalisation
 
... Prednisone increased to >0.5 mg/kg/day
 
... New cyclophosphamide, azathioprine, methotrexate, and mycophenolate used for active SLE
 
... Hospitalization due to active SLE
 
... Physician Global Assessment score (PGA score) increased by > 2.5
 |

Source: [1] Petri M, Kim MY, Kalunian KC, et al. Combined oral contraceptives in women with systemic lupus erythematosus. N Engl J Med. 2005;353 (suppl): 2550 - 2558.

[2] Jill P Buyon, Michelle A Petri, Mimi Y Kim, et al. The effect of combined estrogen and progesterone hormone replacement therapy on disease activity in systemic lupus erythematosus: a randomized trial. Ann Intern Med. 2005 Jun 21;142(12 Pt 1):953-62.

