### **5.3. Efficacy Evaluation**

#### **5.3.1. SELENA-SLEDAI Score**

SELENA-SLEDAI is a validated SLE activity index system used to measure disease activity in SLE patients over the past 10 days, primarily evaluating the presence of 24 clinical characteristics across 9 organ systems. In this index system, the presence of different clinical characteristics is assigned corresponding weighted scores, as detailed in Appendix 2. The total SELENA-SLEDAI score is the sum of the weighted scores corresponding to the 24 clinical characteristics, with a total score range of 0 to 105. The SELENA-SLEDAI score will be assessed by the evaluating physician, with higher total SELENA-SLEDAI scores indicating more severe disease.

SELENA-SLEDAI scores will be assessed at V1 (screening visit), V2 (baseline visit), V4, V6, V8, V10 (EOT visit), V11, V12, V13, and V14 (EOS visit).

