### **5.3.2. SLE Flare/BILAG-2004/PGA Score**

The SLE Flare Index (see Appendix 3) is used to detect SLE flares and distinguish between mild to moderate flares and severe flares.

BILAG-2004 (see Appendix 4) is a validated SLE disease activity index that assesses changes in the patient's clinical manifestations over the past 4 weeks compared to the previous 4 weeks (not present, improving, same, worse, or new), based on the physician's treatment intent, including 97 clinical signs, symptoms, and laboratory parameters across 9 organ systems. A five-level system is used to assess the degree of disease change in all 9 organ systems: A (severe), B (moderate), C (mild), D (inactive), E (inactive with no previous involvement).

The PGA score (see Appendix 5) is the physician's assessment of the overall disease activity in SLE patients over the past 2 weeks, using a visual analog scale to assess disease activity. SLE patients will undergo PGA assessment, with 0 points representing no activity, 1 point representing mild activity, 2.0 to 2.5 points representing moderate activity, and 3 points representing severe activity.

The number of SLE flares and the severity of each flare, as well as the date of each flare, will be recorded at V2 (baseline visit), V4, V6, V8, V10 (EOT visit), V11, V12, V13, and V14 (EOS visit), with the severity of the flare referring to the SLE Flare Scoring Index.

BILAG-2004 scores will be assessed at V2 (baseline visit), V6, V10 (EOT visit), V12, and V14 (EOS visit).

PGA scores will be assessed at V1 (screening visit), V2 (baseline visit), V4, V6, V8, V10 (EOT visit), V11, V12, V13, and V14 (EOS visit).

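### In Appendix 3 the severe-flare PGA item can be met only from a reference PGA below 0.5, and neither SELENA-SLEDAI item states a direction

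*Protocol*

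**What the plan says.** Protocol Section 5.3.2 uses the index in Appendix 3 to detect flares and to separate mild or moderate flares from severe ones. The number, date and severity of flares are recorded at nine visits (V2, V4, V6, V8 and V10 to V14; also Table 1, note 21).

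Two pairs of items in Appendix 3 matter here.

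- **PGA.** Mild/moderate: "An increase of 1.0 or more, but no more than 2.5, in PGA score". Severe: "Physician Global Assessment score (PGA score) increased by" more than 2.5.
- **SELENA-SLEDAI.** Mild/moderate: "A change in SELENA-SLEDAI score of 3 points or more (but not exceeding 12 points". Severe: "SELENA-SLEDAI score change greater than 12".

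Section 5.3.2 describes the PGA scale "with 0 points representing no activity, 1 point representing mild activity, 2.0 to 2.5 points representing moderate activity, and 3 points representing severe activity". Appendix 5 gives the same anchors. Section 5.3.1 describes SELENA-SLEDAI "with a total score range of 0 to 105", and inclusion criterion 3 (Section 3.7.1) requires a screening score above 0 and at most 12.

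Section 2 lists time to first flare as an exploratory endpoint, with no restriction on severity. Section 8.3.4 describes it by Kaplan-Meier methods.

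**The concern.** Two features of the scoring rule do not fit the rest of the document.

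First, the severe PGA item asks for a rise almost as large as the whole scale. A patient who goes from mild activity to the protocol's own severe anchor falls in the mild/moderate band on PGA.

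Second, the SELENA-SLEDAI items are the only score or dose items in the table without a direction: the PGA and prednisone items speak of increases, and the clinical items of new or worsening findings. Elsewhere the protocol uses *change* for this same score as a two-way term, in the change-from-baseline endpoint of Section 2.

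At stake are the severity recorded for each flare and, through the missing direction, the flare events that enter the time-to-first-flare estimate. If improvement were counted as flare, the arm that improves more would collect more false events.

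**Working it through.** The plan gives no figure of its own to reproduce; the check is range arithmetic on the stated scales.

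**1. Reach of the severe PGA item.** Inputs: scale 0 to 3 (Section 5.3.2, Appendix 5); threshold, a rise above 2.5 (Appendix 3). The largest possible rise is 3 minus the reference score.

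| Reference PGA | Largest rise | Rise above 2.5 possible? |
|---|---|---|
| 0 | 3.0 | yes |
| 0.4 | 2.6 | yes |
| 0.5 | 2.5 | no |
| 1 (mild) | 2.0 | no |
| 2 (moderate) | 1.0 | no |

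The condition 3 − reference > 2.5 gives reference < 0.5, which is 0.5/3 = 16.7% of the scale length. This is a share of the scale, not of patients.

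**2. Effect on the endpoint.** As written, the two PGA items together cover every rise of 1.0 or more: 1.0 to 2.5 is mild/moderate, above 2.5 is severe. A rise from 1 to 3 is therefore a flare either way, on the same date. Only its grade is in question.

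**3. Reading the PGA item as a level.** If the item were worded as an increase *to* more than 2.5, it could be met from any reference up to 2.5. The neighbouring prednisone item in the severe column is worded as an increase to a level, and 2.5 is where the PGA anchors pass from moderate to severe. That points to a possible wording slip but does not prove one.

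**4. Direction of the SELENA-SLEDAI items.** The 24 weights in Appendix 2 add up as 8×8 + 6×4 + 7×2 + 3×1 = 64 + 24 + 14 + 3 = 105, which matches the stated range. Every whole score from 1 to 12 is attainable at entry.

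- A fall of 3 or more is possible from scores 3 to 12, that is from 10 of the 12 entry scores. Example: 8 to 4, a fall of 4, meets the mild/moderate item if no direction is read in.
- The largest fall from an entry-range score is 12, so such a fall cannot meet the severe item, which needs more than 12.
- A rise of more than 12 is possible from every entry score: even from 12, the scale leaves 105 − 12 = 93 points.

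**5. Size of one false event.** Section 8.1 plans 8 CM313 subjects per dose level. With all 8 still at risk, one false event moves the estimated flare rate by 1/8 = 12.5 percentage points.

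**6. Reference visit.** Appendix 3 does not say against which visit a rise or change is measured. Appendix 5 compares PGA worsening with the last findings. The choice matters: a subject who enters at PGA 1, improves to 0.3 and then worsens to 3 rises by 2.0 from baseline but by 2.7 from the last visit.

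**The case against.** The case for leaving this alone has several parts.

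- **Severe flare has other routes.** A reader might infer that severe flares as a whole are nearly unreachable. The document does not support that. The severe column also lists new or worsening organ manifestations (with their prednisone or hospitalisation requirement), a prednisone increase, new immunosuppressants, hospitalisation and the SELENA-SLEDAI item. This stands, and it confines the defect to one item.
- **The SELENA-SLEDAI cut-off of 12 is not an error.** A reader might infer that it is, because subjects enter at 12 or below. A rise above 12 is demanding, but it is possible from every entry score. Nothing in the protocol supports turning this item into a level.
- **Context implies worsening.** The items stand under flare headings, physicians judge and record each flare, and no text directs that improvement be counted. A clinician would probably not record 8 to 4 as a flare. This lowers the likelihood of miscounting, but a scoring rule, and any edit check built from it, should not depend on inference when its neighbours state the direction.
- **The endpoint is exploratory and descriptive.** Section 8.3.4 names no analysis by severity. This stands and limits the consequence.
- **The cited instrument is not at hand.** Whether it says *by* or *to* cannot be settled from the protocol. This also stands, so the fix asks for a check and does not presume the answer.

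**Conclusion.** The point holds in a limited form. The severe PGA item can be met only from a reference PGA below 0.5, so on the PGA items worsening from mild to severe is graded mild or moderate. As the item stands, that affects recorded severity, not time to first flare. Both SELENA-SLEDAI items lack a direction; read literally, an improvement of 3 to 12 points meets the mild/moderate item and could add false events to an exploratory estimate, at 12.5 percentage points per event in a group of 8.

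The documents do not show that improvement was meant to count as flare; this is a wording defect open to misreading. The primary safety objective is not touched.

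Assumptions: PGA is scored continuously or in small steps from 0 to 3 (the scale figure is not shown), and the entries in each column of Appendix 3 are alternatives, which the layout suggests but no sentence states. The distribution of baseline PGA is not given, so the share of subjects affected is unknown.

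**What to change.** In Appendix 3:

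1. Reconcile the severe PGA item with the 0-to-3 scale and with the instrument cited under the table, and settle whether it means a rise *by* or a rise *to* more than 2.5. The answer should be fixed before flares are analysed. Under a level reading, a rise of less than 1.0 that ends above 2.5 (for example 2.0 to 2.6) would newly count as a flare, so event dates could then change too.
2. Replace *change* with *increase* in both SELENA-SLEDAI items, and keep the 3- and 12-point cut-offs.
3. State the reference visit for the score items.
4. Carry the same wording into the eCRF completion guidance, because the grading is done at the visit.

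The cost is a few words in an appendix and in the eCRF guidance, handled as a protocol amendment under Section 11.7, plus a recheck of any flares already graded. Version 2.0 made the same kind of correction to Appendices 2 and 4 against the English scales; its summary of changes lists none for Appendix 3.

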## Appendix 4 BILAG-2004 Score

BILAG-2004 assesses the disease activity status of each organ system in the past 4 weeks, involving 9 organ systems: constitutional, mucocutaneous, neuropsychiatric, renal, hematologic, musculoskeletal, cardiorespiratory, gastrointestinal, and ocular.

### BILAG-2004 Assessment Criteria

| Grade | Definition                                                                                                                                                                                                                                                                                                                                                                                                                                                                             |
|-------|----------------------------------------------------------------------------------------------------------------------------------------------------------------------------------------------------------------------------------------------------------------------------------------------------------------------------------------------------------------------------------------------------------------------------------------------------------------------------------------|
| A     | Severe disease activity requiring any of the following treatment:
1. systemic high-dose oral corticosteroids (equivalent to prednisolone > 20 mg/day)
2. intravenous pulse glucocorticoids (equivalent to pulse methylprednisolone ≥ 500 mg)
3. systemic immunomodulators (include biologicals, immunoglobulins and plasmapheresis)
4. therapeutic high-dose anticoagulation in the presence of high-dose steroids or immunomodulators; e.g., warfarin with target INR 3-4 |
| B     | Moderate disease activity requiring any of the following treatment:
1. systemic low-dose oral glucocorticoids (equivalent to prednisone ≤ 20 mg/day)
2. intramuscular or intra-articular or soft tissue glucocorticoids injection (equivalent to methylprednisolone < 500 mg)
3. topical glucocorticoids
4. topical immunomodulators
5. antimalarials or thalidomide or prasterone or acitretin
6. symptomatic therapy; e.g., NSAIDs for inflammatory arthritis      |
| C     | Mild                                                                                                                                                                                                                                                                                                                                                                                                                                                                                   |
| D     | Inactive but previously affected                                                                                                                                                                                                                                                                                                                                                                                                                                                       |
| E     | Inactive with no previous involvement                                                                                                                                                                                                                                                                                                                                                                                                                                                  |

Source: Chee-Seng Yee, Vernon Farewell, David A Isenberg, et al. The BILAG-2004 index is sensitive to change for assessment of SLE disease activity. Rheumatology 2009;48: 691-695

### BILAG-2004 Assessment Scale

Only record manifestations/items due to SLE disease activity, and assessment refers to manifestations occurring in the last 4 weeks (compared with the previous 4 weeks).

|                                                                                                                                                                                                                                                                                                                                                                                                                                                                                                                                                                                                                                                                                                                                                                                                                                                                                                                                                                                                                                                                                                                                                                                                                           |                                                                                                                                                                                                                                                                                                                                                                                                                                                                                                                                                                                                                                                                                                                                                                                                                                                                                                                                                                                                                                                                                                                                                                                                                                                                                                                                                                                                                                                                                                                                                                                                                                                                                                                                                                     |
|---------------------------------------------------------------------------------------------------------------------------------------------------------------------------------------------------------------------------------------------------------------------------------------------------------------------------------------------------------------------------------------------------------------------------------------------------------------------------------------------------------------------------------------------------------------------------------------------------------------------------------------------------------------------------------------------------------------------------------------------------------------------------------------------------------------------------------------------------------------------------------------------------------------------------------------------------------------------------------------------------------------------------------------------------------------------------------------------------------------------------------------------------------------------------------------------------------------------------|---------------------------------------------------------------------------------------------------------------------------------------------------------------------------------------------------------------------------------------------------------------------------------------------------------------------------------------------------------------------------------------------------------------------------------------------------------------------------------------------------------------------------------------------------------------------------------------------------------------------------------------------------------------------------------------------------------------------------------------------------------------------------------------------------------------------------------------------------------------------------------------------------------------------------------------------------------------------------------------------------------------------------------------------------------------------------------------------------------------------------------------------------------------------------------------------------------------------------------------------------------------------------------------------------------------------------------------------------------------------------------------------------------------------------------------------------------------------------------------------------------------------------------------------------------------------------------------------------------------------------------------------------------------------------------------------------------------------------------------------------------------------|
| 
Scoring Criteria
 
0 Not present
 
1 Improving
 
2 Same
 
3 Worse
 
4 New
 
or ND not done
 
or Enter laboratory value at designated location
 
or Yes/No
 
*Yes/No Circle "Yes" or "No" to indicate whether the abnormal value is caused by SLE.
                                                                                                                                                                                                                                                                                                                                                                                                                                                                                                                                                                                                                                                                                                                                                                                                                                                                                                              | 
Cardiopulmonary
 
44. Myocarditis - mild ( )
 
45. Myocarditis/endocarditis + cardiac failure ( )
 
46. Arrhythmia ( )
 
47. New valvular dysfunction ( )
 
48. Pleurisy/pericarditis ( )
 
49. Cardiac tamponade ( )
 
50. Pleural effusion with dyspnoea ( )
 
51. Pulmonary haemorrhage/vasculitis ( )
 
52. Interstitial alveolitis/pneumonia ( )
 
53. Shrinking lung syndrome ( )
 
54. Aortitis ( )
 
55. Coronary vasculitis ( )
 
Gastrointestinal
 
56. Lupus peritonitis ( )
 
57. Abdominal serositis or ascites ( )
 
58. Lupus enteritis/colitis ( )
 
59. Malabsorption ( )
 
60. Protein-losing enteropathy ( )
 
61. Intestinal pseudo-obstruction ( )
 
62. Lupus hepatitis ( )
 
63. Acute lupus cholecystitis ( )
 
64. Acute lupus pancreatitis ( )
 
Ophthalmic
 
65. Orbital inflammation/myositis/proptosis ( )
 
66. Keratitis - severe ( )
 
67. Keratitis - mild ( )
 
68. Anterior uveitis ( )
 
69. Posterior uveitis/retinal vasculitis - severe ( )
 
70. Posterior uveitis/retinal vasculitis - mild ( )
 
71. Episcleritis ( )
 
72. Scleritis - severe ( )
 
73. Scleritis - mild ( )
 
74. Retinal/choroidal vaso-occlusive disease ( )
 
75. Isolated cotton-wool spots (cytoid bodies) ( )
 
76. Optic neuritis ( )
 
77. Anterior ischaemic optic neuropathy ( )
 
Renal
 
78. Systolic blood pressure (abnormal value > 140 mm Hg) value ( ) Yes/No*
 
79. Diastolic blood pressure (abnormal value > 90 mm Hg) value ( ) Yes/No*
 
80. Accelerated hypertension Yes/No ( )
 |
| 
Constitutional
 
1. Pyrexia - documented >37.5°C ( )
 
2. Weight loss - unintentional >5% ( )
 
3. Lymphadenopathy/splenomegaly ( )
 
4. Anorexia ( )
 
Mucocutaneous
 
5. Skin eruption - severe ( )
 
6. Skin eruption - mild ( )
 
7. Angio-oedema - severe ( )
 
8. Angio-oedema - mild ( )
 
9. Mucosal ulceration - severe ( )
 
10. Mucosal ulceration - mild ( )
 
11. Panniculitis/Bullous lupus - severe ( )
 
12. Panniculitis/Bullous lupus - mild ( )
 
13. Major cutaneous vasculitis/thrombosis ( )
 
14. Digital infarcts or nodular vasculitis ( )
 
15. Alopecia - severe ( )
 
16. Alopecia - mild ( )
 
17. Periungual erythema/chilblains ( )
 
18. Splinter haemorrhage ( )
 
Neuropsychiatric
 
19. Aseptic meningitis ( )
 
20. Cerebral vasculitis ( )
 
21. Demyelinating syndrome ( )
 
22. Myelopathy ( )
 
23. Acute confusional state ( )
 
24. Psychosis ( )
 
25. Acute inflammatory demyelinating polyradiculoneuropathy ( )
 
26. Mononeuropathy (single/multiplex) ( )
 
27. Cranial neuropathy ( )
 |                                                                                                                                                                                                                                                                                                                                                                                                                                                                                                                                                                                                                                                                                                                                                                                                                                                                                                                                                                                                                                                                                                                                                                                                                                                                                                                                                                                                                                                                                                                                                                                                                                                                                                                                                                     |

|                                                       |                                                                                           |
|-------------------------------------------------------|-------------------------------------------------------------------------------------------|
| 28. Plexopathy ( )                                    | 81. Urine dipstick protein (+=1, ++=2, +++=3) value ( ) Yes/No*                           |
| 29. Polyneuropathy ( )                                | 82. UACR (mg/mmol) value ( ) Yes/No*                                                      |
| 30. Seizure disorder ( )                              | 83. UPCR (mg/mmol) value ( ) Yes/No*                                                      |
| 31. Status epilepticus ( )                            | 84. 24-hour urine protein (g) value ( ) Yes/No*                                           |
| 32. Cerebrovascular disease (not due to vasculitis)   | 85. Nephrotic syndrome Yes/No ( )                                                         |
| 33. Cognitive dysfunction ( )                         | 86. Creatinine (plasma/serum: abnormal value >130 $\mu$ mol/L) value ( ) Yes/No*          |
| 34. Movement disorder ( )                             | 87. GFR (abnormal value < 80 mL/min/1.73 m  ) value ( ) Yes/No*               |
| 35. Autonomic disorder ( )                            | 88. Active urinary sediment Yes/No ( )                                                    |
| 36. Cerebellar ataxia (isolated) ( )                  | 89. Active nephritis Yes/No ( )                                                           |
| 37. Lupus headache - severe unremitting ( )           | Haematological                                                                     |
| 38. Headache from IC hypertension ( )                 | 90. Haemoglobin (abnormal value $\leq$ 10.9 g/dL) value ( ) Yes/No*                       |
| Musculoskeletal                                | 91. Total white cell count (abnormal value $\leq$ $3.9 \times 10^9$ /L) value ( ) Yes/No* |
| 39. Myositis severe ( )                               | 92. Neutrophils (abnormal value $\leq$ $1.9 \times 10^9$ /L) value ( ) Yes/No*            |
| 40. Myositis - mild ( )                               | 93. Lymphocytes (abnormal value $\leq$ $1.0 \times 10^9$ /L) value ( ) Yes/No*            |
| 41. Arthritis (severe) ( )                            | 94. Platelets (abnormal value $\leq$ $149 \times 10^9$ /L) value ( ) Yes/No*              |
| 42. Arthritis (moderate)/tendonitis/tenosynovitis ( ) | 95. TTP records 0, 1, 2, 3, 4.                                                            |
| 43. Arthritis (mild)/arthralgia/myalgia ( )           | 96. Evidence of active hemolysis Yes/No ( )                                               |
|                                                       | 97. Coomb's test positive (isolated) Yes/No ( )                                           |

Abbreviations: GFR=glomerular filtration rate; TTP=thrombotic thrombocytopenic purpura; UACR=urine albumin/creatinine ratio; UPCR=urine protein/creatinine ratio.

